### Vi-Typhoid Conjugate Vaccine Dose

Typbar-TCV is a Vi-TCV vaccine manufactured by Bharat Biotech International (Hyderabad, India) that consists of 25 μg of Vi polysaccharide conjugated to a nontoxic tetanus toxoid protein carrier. It is given as a 0.5 ml dose by the intramuscular route to infants, toddlers, children, and adults. This vaccine will be shipped from the manufacturer in 5-dose, 2.5 mL vials.

### Inactivated Poliovirus Vaccine Dose

The control vaccine for this study is Inactivated Poliovirus Vaccine (IMOVAX POLIO, Sanofi Pasteur, Lyon, France). This vaccine consists of 40 D-antigen units (DU) of Poliovirus type 1, 8 DU of Poliovirus type 2, and 32 DU of Poliovirus type 3 preserved in 2-phenoxyethanol (5 mg/mL). IPV is given as a 0.5 ml dose by the intramuscular route to infants, toddlers, children, and adults.

### Study Population

Children aged 9–11 months and 15–23 months may enroll, provided they fulfill all inclusion and exclusion criteria (Table 2) and that their parent/guardian completes the informed consent process. The study recruits participants from Schiphra Medical Center in Ouagadougou, Burkina Faso.

**Table 2. T2:** Study Inclusion and Exclusion Criteria

**Inclusion Criteria**	1. A healthy male or female child, either between the ages of 9–11 months or 15–23 months at the time of study vaccination. 2. A child whose parent/guardian resides primarily within the Ouagadougou study area at the time of study vaccinations and who intends to be present in the area for the duration of the trial. 3. A child whose parent/guardian has voluntarily given informed consent.
**Exclusion Criteria**	1. A history of documented hypersensitivity to any vaccine component. 2. Prior receipt of any typhoid vaccine. 3. For children 9–11 months, prior receipt of yellow fever vaccine or any measles-rubella–containing vaccine. 4. For children 15–23 months, prior receipt of meningococcal A conjugate vaccine or a second measles-rubella vaccine. 5. Prior receipt of any measles-rubella–containing vaccine (for children 9–11 months). 6. A history of severe allergic reaction with generalized urticarial, angioedema, or anaphylaxis. 7. A known history of diabetes, tuberculosis, cancer, chronic kidney disease, heart disease, liver disease, a progressive neurological disorder, poorly controlled seizures, or a terminal illness. 8. Severe malnutrition, as determined by mid-upper arm circumference (MUAC) < 12.5 cm. 9. Receipt of any other investigational intervention in the last 6 months or anticipated receipt during the course of the study. 10. Receipt of blood products in the last 6 months. 11. A known human immunodeficiency virus infection or exposure, or other immunosuppressive conditions. 12. Receipt of systemic immunosuppressant or systemic corticosteroids. 13. Any condition determined by the investigator to be likely to interfere with evaluation of the vaccine, to be a significant potential health risk to the child, or to make it unlikely that the child would complete the study.

## STUDY PROCEDURES

### Recruitment and Screening

Following community sensitization using Institutional Review Board (IRB)-approved materials, local community families with children aged 9–11 months and 15–23 months will be given study information in French and/or a local language (including Mossi, Dyula, and Fulani), either individually or in a group setting. The voluntary nature of the study and the right to withdraw will be explained. Parents of eligible children will then be encouraged to ask questions and will provide written informed consent in a semi-private area before enrollment and vaccination. The consent form will have a signature or thumbprint from the child’s parent/guardian before any study procedure. The adult literacy rate in Burkina Faso was 35% in 2014 [13], and providing a thumbprint is a locally acceptable equivalent for a written signature. A copy will be given to the parent/guardian and another copy will be filed on site. If a parent/guardian is unable to read or sign, an impartial witness will document that all information was provided and consent was freely given. After informed consent is obtained, each potential participant will be screened for eligibility, according to the inclusion/exclusion criteria.

### Randomization

Randomization will be computer-generated to allocate eligible participants in a 1:1 ratio for the 9–11-month-old cohort or a 1:1:1 ratio for the 15–23-month-old cohort, using stratified block randomization with varying block sizes from 6–12.

### Blinding

Vi-TCV and IPV have similar pharmaceutical presentations. Unblinded study personnel will be responsible for vaccine preparation and administration. These unblinded personnel will not be involved in study-related assessments or have contact with subjects for the purpose of data collection following the study vaccination. Study participants, their family members, and study staff will not know the assigned vaccine group. The 15–23-month-old cohort will be unblinded on Day 28, so that Group 3 can receive MCV-A at this visit.

### Enrollment

Screening and enrollment visits may occur on the same day. Study staff will review the participant’s eligibility criteria, medical history, concomitant medications, and vaccination history. All participants will have their temperature taken and 3–5 mL of blood drawn for baseline immunogenicity and *P. falciparum* malaria parasitemia testing. Participants will be administered both the study and routine vaccinations (Figure 1), then asked to remain in the study area for at least 30 minutes in case of a serious reaction. Any immediate reactions will be assessed and recorded.

**Figure 1. F1:**
[figure not shown]
Trial flow diagram. EPI, Expanded Program on Immunization; IPV, inactivated poliovirus vaccine; MCV-A, meningococcal A conjugate vaccine; MR, measles-rubella vaccine; Vi-TCV, Vi-typhoid conjugate vaccine; YFV, yellow fever vaccine.

### Follow-up

Follow-up visits may be either routine or unscheduled. Routine visits will occur on Days 3, 7, 28, and 180. On Days 3 and 7 following vaccination, participants will be asked to return to the study clinic to assess reactogenicity. During these visits, solicited and unsolicited AEs will be recorded. Alternatively, these visits may be conducted in the home. On Day 28 following vaccination, participants will be asked to return to the study clinic for a follow-up visit. During this visit, the treatment groups in the 15–23-month-old cohort will be unblinded, participants will have approximately 3–5 mL of blood drawn to measure the Vi antibody responses for typhoid (all age groups), measure the TT serum IgG antibody levels (all age groups), and conduct the yellow fever plaque reduction neutralization testing (9–11-month-old group only) or measure the meningococcal A serum bactericidal antibody titers (15–23-month-old group only), which will be used for the primary and secondary objectives, as listed. Participants will have their final visit on Day 180, when interim SAEs will be recorded.

During unscheduled visits, participants will undergo standard procedures for the evaluation and treatment of illness, as defined by the Ministry of Health. Illnesses and other medical issues will be documented as AEs in participant records, and their seriousness, severity, relationship to the study product, and expectedness will be recorded.

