## TRIAL OVERVIEW

A randomized, controlled, Phase II trial will test Vi-TCV co-administration with vaccinations routinely given at 9 and 15 months of age in Burkina Faso. Our aim is to assess the safety and immunogenicity of Vi-TCV when co-administered with vaccinations routinely given to children at both 9 and 15 months of age in Burkina Faso. The Vi-TCV vaccine or an inactivated poliovirus vaccine (IPV) will be administered. Children 9–11 months of age will be randomized 1:1 to Vi-TCV or IPV; children 15–23 months of age will be randomized 1:1:1 to Vi-TCV + MCV-A, Vi-TCV + IPV with delayed MCV-A, or MCV-A + IPV. We will use block randomization with varying block sizes from 6–12. Our study objectives and endpoints are listed in Table 1.

**Table 1. T1:** Primary, Secondary, and Exploratory Objectives and Endpoints

	Objectives	Endpoints
**Primary**	To assess the safety of Vi-TCV when co-administered with Expanded Program on Immunization vaccines among children 9–11 months of age and 15–23 months of age in Burkina Faso.	1. Proportion of participants who develop adverse events in the first 30 minutes after vaccination and for 7 days after vaccination. 2. Proportion of participants who experience SAEs within 6 months of vaccination, in all participants. 3. Proportion of participants who experience other, non-serious adverse events up to 28 days following vaccination.
**Secondary**	1. To assess the immunogenicity of YFV when given with and without Vi-TCV in children 9–11 months of age. 2. To assess the immunogenicity of MCV-A when given with and without Vi-TCV in children 15–23 months of age. 3. To assess the immunogenicity of Vi-TCV when given with YFV in children 9–11 months of age. 4. To assess the immunogenicity of Vi-TCV when given with and without MCV-A in children 15–23 months of age.	1. Immunogenicity of YFV: yellow fever plaque reduction neutralization test at Days 0 and 28 in infants 9–11 months of age. 2. Immunogenicity of MCV-A: serum bactericidal antibody assay against *Neisseria meningitidis* serogroup A at Days 0 and 28 in children 15–23 months of age. 3. Immunogenicity of Vi-TCV when given with YFV: anti-Vi IgG antibody titer, as measured by ELISA at Days 0 and 28 in infants 9–11 months of age. 4. Immunogenicity of Vi-TCV when given with and without MCV-A: anti-Vi IgG antibody titer, as measured by ELISA at Days 0 and 28 in infants 9–11 months of age.

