## METHODS

This study will be divided into 2 cohorts, by age, with separate study designs. Cohort 1 will include children 9–11 months of age. Cohort 2 will include children 15–23 months of age. The purpose for our detailed evaluation of safety and immunogenicity is to assess vaccine reactogenicity and the immune response to Vi-TCV and co-administered vaccines. Serum will be collected from all participants on Day 0 (before vaccination) and on post-vaccination Day 28 to quantify anti-Vi and anti-TT antibodies. All children will have an additional 0.5 mL of blood collected on Day 0, before the study vaccination, to test for the presence of malaria parasitemia at baseline. Some studies demonstrate impaired immunogenicity of routine vaccinations in children with *Plasmodium**falciparum* malaria at sites similar to Ouagadougou [10–12], and we will evaluate this potential effect by measuring for *P. falciparum* parasitemia on Day 0.

Children 9–11 months of age will be eligible for Cohort 1, a double-blind, individually randomized, controlled trial. Up to 100 children will be randomized in a 1:1 ratio to receive Vi-TCV (Group 1) or IPV (Group 2). Participants and parents will not know the study vaccine received. Vi-TCV or IPV will be administered with MR and YFV, as per Burkina Faso’s EPI schedule. These 9–11-month-old children will have immunogenicity to Vi-TCV, YFV, and TT assessed on Days 0 and 28.

Children 15–23 months of age will be eligible for Cohort 2, a randomized safety and immunogenicity study of (1) Vi-TCV when co-administered with routine EPI vaccines (MCV-A and MR) or given alone and (2) MCV-A when co-administered or given alone. Participants in this cohort (up to 150) will be randomized 1:1:1: Group 3 participants will receive Vi-TCV and IPV at Day 0, with a subsequent dose of MCV-A at Day 28; Group 4 will receive MCV-A and Vi-TCV at Day 0; and Group 5 will receive MCV-A and IPV at Day 0. All children will receive MR at Day 0. Cohort 2 will be unblinded on Day 28 for safety and follow-up and to ensure MCV-A receipt in Group 3. These 15–23-month-old children will have serum bactericidal antibodies to *Neisseria meningitidis* serogroup A, anti-Vi antibody, and TT antibody assessed on Days 0 and 28.

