We will measure anti-Vi immunoglobulin G (IgG) antibody responses using the VaccZyme Salmonella typhi Vi IgG enzyme-linked immunosorbent assay commercial kit (The Binding Site Group Ltd, Birmingham, UK). Antibody titers will be expressed as enzyme-linked immunosorbent assay units per milliliter (U/mL). Both anti-Vi IgG antibody geometric mean titers and seroconversion, defined as a 4-fold or greater rise in anti-Vi antibody titers from baseline, will be calculated per group. The difference in geometric mean titers between the 2 groups will be compared using a 2-sample Student *t* test on log-transformed titers or a Mann-Whitney U test, as appropriate. The difference in the percentages of participants who seroconverted between the 2 groups will be compared using the Pearson’s chi-square test or Fisher’s exact test, as appropriate.

Participants in both cohorts will have home or clinic visits on Days 3 and 7 following vaccination, for local and systemic adverse event (AE) capture. Non-serious AEs will be assessed up to Day 28. Serious adverse events (SAEs) will be captured throughout the study follow-up.

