### Note on Timing

All solicited and unsolicited AEs occurring through Day 7 post-vaccination will be assessed and recorded. All AEs that meet the criteria for an SAE and that occur through 6 months post-vaccination will be assessed and recorded.

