^b^Confirm informed consent for study procedures.

^c^Review/confirm information or activity in participants previously consented and screened.

^d^Participants must not eat or drink anything hot or cold within 10 minutes before taking oral temperature.

^e^Prior to study vaccination and used as a baseline.

^˚^Targeted physical exam if indicated based on interim medical history.

^f^Only for children in Group 3 in the 15 through 23 month old cohort

^g^3-5m1 of blood collected for immunogenicity and noninterference testing ^h^If AE/SAE occurs post-vaccination

^i^Only if visit occurs within 7 days after study vaccination.

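### Cohort 2 is unblinded at the visit that must supply the Day 8–28 adverse events of primary endpoint 3, with no stated safeguard that keeps the review blind; the same visit's window also lets Group 3's MCV-A fall just inside the 28 days

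*Protocol article*

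**What the plan says.** Table 1 (Trial Overview) defines primary endpoint 3 as "Proportion of participants who experience other, non-serious adverse events up to 28 days following vaccination", and Methods agrees: "Non-serious AEs will be assessed up to Day 28". The Note on Timing gives a shorter limit: "All solicited and unsolicited AEs occurring through Day 7 post-vaccination will be assessed and recorded". The Definition of Adverse Event section also refers only to the first 7 days.

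In Cohort 2, Methods states that "Group 3 participants will receive Vi-TCV and IPV at Day 0, with a subsequent dose of MCV-A at Day 28". The Blinding section gives the reason for opening the code: "The 15–23-month-old cohort will be unblinded on Day 28, so that Group 3 can receive MCV-A at this visit". The Follow-up section describes the Day 28 visit as follows: "During this visit, the treatment groups in the 15–23-month-old cohort will be unblinded, participants will have approximately 3–5 mL of blood drawn". Table 4 sets this visit, V04, at Day 28 ±3 and marks vaccination there with footnote f: "Only for children in Group 3 in the 15 through 23 month old cohort". The next routine contact is Day 180: "Participants will have their final visit on Day 180, when interim SAEs will be recorded".

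The Analysis section analyses children as randomized and keeps all follow-up time from randomization.

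**The concern.** Two features of V04 bear on the same primary safety endpoint.

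- **Blinding of the review.** The visit that closes the 28-day event history is also the visit at which parents and staff learn the group. If the history is taken after that, what parents recall and how staff grade severity and relatedness can depend on the allocation. This needs no early visit and applies to Groups 3, 4 and 5 alike. The documents do not show which way such a bias would run. An analysis rule written later cannot restore blinding lost at data collection.
- **A second vaccine inside the window.** A Group 3 child seen before Day 28 can receive MCV-A while the endpoint-3 clock is still running. Groups 4 and 5 received MCV-A on Day 0 and get nothing at V04. Any recorded reaction would sit in Group 3's proportion. Group 3 is the comparator for Group 4, so this would narrow an apparent excess with co-administration.

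**Working it through.** **1. The plan's nearest figure.** Table 3 states 80% power for Group 3 against Group 4 (10% v 33%, 45 per group, two-sided 5%, unpooled z-test).

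- Evaluable children: 150 × 0.90 / 3 = 45 per group.
- Standard error: √[(0.10 × 0.90 + 0.33 × 0.67) / 45] = √(0.3111 / 45) = 0.08315.
- Power: Φ(0.23 / 0.08315 − 1.96) = Φ(0.806) = 79.0%, which agrees with 80% after rounding of the detectable difference.

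This outcome covers 7 days after vaccination, and MCV-A at V04 comes no earlier than Day 25, so the figure is untouched. The article gives no hypothesis or power figure for endpoint 3.

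**2. Where Day 8–28 events can be recorded (Table 4 and Follow-up).**

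- V03, Day 7 ±1: last scheduled reactogenicity and solicited-event assessment.
- V04, Day 28 ±3: medical history and medication review, blood draw, unblinding, and MCV-A for Group 3.
- V05, Day 180 ±7: medical history is ticked, but the text gives the purpose as SAEs, and Cohort 2 is already unblinded.
- Unscheduled visits: illnesses are documented as adverse events.

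V04 is therefore the only routine contact at which the Day 8–28 part of endpoint 3 could be collected blind, and it is the visit at which the blind ends.

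**3. Overlap with MCV-A.** For a V04 on day v, the elapsed window time after MCV-A is max(0, 28 − v):

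- Day 25: 3 days
- Day 26: 2 days
- Day 27: 1 day
- Day 28: 0 (same date only)
- Days 29–31: none

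**4. Size of the overlap effect.** Endpoint 3 is a proportion of children, so a reaction adds a case only in a child with no earlier counted event. The rise in Group 3 is c × f × r × (1 − b), where:

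- c is the share of reactions captured;
- f is the share of Group 3 given MCV-A before Day 28;
- r is the reaction rate by Day 28;
- b is the background 28-day event proportion.

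The documents give none of these. Assumed values are r = 5–10% and b = 20–50%.

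- Visits spread evenly over Days 25–31 (f = 3/7) and full capture (c = 1): low 3/7 × 0.05 × 0.50 = 1.1 points; high 3/7 × 0.10 × 0.80 = 3.4 points. That is 0.5 to 1.5 children of 45.
- Every visit on Days 25–27 (f = 1), c = 1: 1 × 0.05 × 0.50 = 2.5 points to 1 × 0.10 × 0.80 = 8 points, or 1.1 to 3.6 children of 45. This is an extreme case.
- No routine capture after V04 (c close to 0): close to zero.

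Table 4 points to a small c. After V04 it schedules no reactogenicity or solicited-event assessment except at an early-termination visit, and the 30-minute evaluation is ticked only on Day 0.

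**The case against.** A reader might infer that reactions to the delayed MCV-A are in fact charged to Vi-TCV + IPV and hide a true excess in Group 4. Taking 3/7 of 50 children (about 21) with a 10–20% reaction rate gives 2 to 4 events, or 4 to 8 points. The documents do not support that. It needs full capture, which Table 4 does not schedule, and it treats every reaction as a new case, although a child with an earlier event adds nothing to a proportion of participants. Such events would enter mainly through unscheduled visits, or through the general 30-minute observation rule if that applies at V04. This part of the objection stands.

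A reader might also infer from the Follow-up sentence that the code must be opened before anything else. It is a list, it does not mention MCV-A, and it sets no sequence. Nor does its order cause the overlap, which comes from the ±3-day window combined with same-visit vaccination. This stands too. What remains is that unblinding is named first and no stated order protects the review.

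A third argument is that visit order and event cut-offs belong to the full protocol or the analysis plan, to which the article defers further detail. That has some force for the cut-off. It does not dispose of the point, because the article itself fixes same-visit unblinding, the window and the 28-day count, and these collide when followed as written. The Blinding section does keep the unblinded vaccine staff away from later assessments. That gives no protection once the cohort's groups are opened at V04.

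**Conclusion.** The point holds in two parts of unequal weight.

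- **Main part.** In Cohort 2, the Day 8–28 component of primary endpoint 3 may be ascertained with the group known, in all three groups (150 children). This follows from the stated visit schedule and needs no assumed rates. Its size cannot be derived from the documents.
- **Secondary part.** Up to 3 elapsed days of Group 3's window can follow MCV-A. Events in that time can, but need not, be counted against Vi-TCV + IPV. The effect is probably small: near zero without routine capture, and about 1–3 points with full capture, evenly spread visits, r = 5–10% and b = 20–50%, all assumed.

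Both parts depend on events being collected to Day 28, as Table 1 and Methods say. If the Day 7 limit in the Note on Timing governs, Days 8–28 are not recorded and endpoint 3 cannot be computed as defined. That contradiction needs resolving in its own right. The reactogenicity comparisons powered in Table 3 are unaffected.

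**What to change.** For Cohort 2 at V04:

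1. Complete the adverse-event, history and medication review and the blood draw before the code is opened and MCV-A is given.
2. End endpoint 3 in all three groups at that blinded review or at Day 28, whichever is earlier.
3. List events after Group 3's MCV-A separately.
4. Reconcile the Day 7 recording limit in the Note on Timing with the Day 28 limit in Table 1 and Methods.

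Item 1 has to be in the conduct documents before V04 visits begin. Item 2 amends the wording of a primary endpoint, so it should be settled before any comparison of groups.

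The cost is a line on visit order and a sentence in the endpoint definition. Children seen before Day 28 lose up to 3 of 28 days of event time (3/28 = 10.7%), so windows vary between 25 and 28 days. The rule and visit window are the same in every Cohort 2 group. No vaccination or its timing changes.

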## ADVERSE EVENTS

### Immediate Reactions

All participants will be observed for immediate reactions for 30 minutes after vaccination. Immediate reactions will be assessed by a study physician or appropriately trained medical staff member, and recorded on the appropriate case report form (CRF).

### Solicited Local and Systemic Reactions

On Day 3, participants will be assessed for local and systemic reactions and will be asked about any events after vaccination on Day 0 and any current symptoms; on Day 7, participants will be assessed for local and systemic reactions and will be asked about current symptoms. Using a standardized data collection instrument, the following local and systemic reactions will be documented and graded on predefined scales, based on a functional assessment or the magnitude of the reaction: fever, injection site pain/tenderness, swelling, erythema, and irritability.

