### Analysis

Study hypotheses and power analyses are found in Table 3. The intention-to-treat population includes all randomized individuals, in the vaccine groups to which they were assigned, and all follow-up time, beginning with the time of randomization. The primary analysis will be based on this population. The per-protocol population includes all vaccinated individuals, in the vaccine groups based on the vaccines they received. Additional details of study analyses will be included in a statistical analysis plan, which will be written by the study biostatistician before the study’s data analysis begins.

**Table 3. T3:** Study Hypotheses and Power Analyses.

	Hypothesis	Power Analysis
**Cohort 1:** Children 9–11 months of age (n = 100), enrolled in a double-blind, individually randomized, controlled trial. With an expected 10% dropout rate, we anticipate 90 children (90% of 100 enrolled) will complete follow-up assessments: 45 in Group 1 and 45 in Group 2.	Reactogenicity following Vi-TCV given together with YFV and MR (Group 1) is not significantly different from reactogenicity following IPV given together with YFV and MR (Group 2).	The expected incidence of any grade 2 or greater solicited, systemic adverse events over 7 days following vaccination is 10% in Group 2 [14]. Sample sizes of 45 in Group 1 and 45 in Group 2 achieve 80% power to detect a minimum difference of 0.23 (= 33% - 10%), using a 2-sided z-test with unpooled variance and a significance level of 5% (PASS 15).
	The percentage of participants with seroconversion (≥2-fold rise) in yellow fever neutralizing antibodies following a single dose of Vi-TCV given together with YFV and MR (Group 1) is not significantly different from the percentage of participants with seroconversion (≥2-fold rise) in yellow fever neutralizing antibodies following a single dose of IPV given together with YF and MR (Group 2).	In Group 2, the expected seroconversion proportion is 70% [14]. Sample sizes of 45 in Group 1 and 45 in Group 2 achieve 80% power to detect a minimum difference of 0.28 (= 70% - 42%), using a 2-sided z-test with unpooled variance and a significance level of 5% (PASS 15).

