## DISCUSSION

This randomized, controlled clinical trial among infants and young children in Ouagadougou, Burkina Faso, will be the first in West Africa to test the pre-qualified Typbar-TCV. The study will provide the first information on co-administration of this vaccine with YFV and MCV-A, as recommended by the WHO. The rationale for the 3 arms in the older children is that both MCV-A and TCV contain tetanus toxoid as the carrier protein: thus, our study design allows us to carefully assess reactogenicity when those vaccines are given alone or together, and evaluate any effect on the antibody responses that might occur with a shared carrier protein. Such a phenomenon was noted with *Haemophilus Influenzae* Type b vaccines [18] and is thought to occur due to interference by a common protein carrier with common immunogenic epitopes [19]. We did not include an assessment of measles and rubella antibody responses, since this has been previously tested and we have attempted to minimize blood collection volumes in these young children.

Malaria parasitemia is prevalent among young children in Burkina Faso. We will test for *P. falciparum* parasitemia at Day 0 to evaluate the potential effect on the immunogenicity of Typbar-TCV and of the other vaccines administered.

**Table 4. T4:** Trial Schedule of Events. Abbreviations: AE, adverse event; SAE, serious adverse event.

Study Visit Type	Recruitment	Screening	Eligibility, enrollment, vaccination	Follow up	Follow up	Follow up	Follow up	Early termination
Study Visit Number		V00	V01	V02	V03	V04	V05	
Study Time point			D0	D3	D7±1	D28±3	D180±7	
Study introduction, recruiting	X	X^a^	X^a^					
Obtain informed consent		X	X^a,b^					
Review eligibility criteria		X	X^a,c^					
Review medical history		X	X^a,c^	X^c^	X^c^	X^c^	X^c^	X^c^
Review concomitant meds		X	X^a,c^	X^c^	X^c^	X^c^	X^c^	X^c^
Review vaccination history		X	X^a,c^	X^c^	X^c^	X^c^		X^c^
Axillary temperature^d^		X	X^e^			X		X
Height and weight and Middle Upper Arm Circumference (MUAC)		X	X^e^				X	X
Targeted physical exam		X^˚^	X^a,c,e,˚^			X^c,˚^		X^c,˚^
Vaccination			X			X^f^		
30-min post-vaccination evaluation			X					
Post-vaccination reactogenicity assessment				X	X			X
Venous blood collection for immunogenicity			X^e,g^			Xg		X^g^
Venous blood collection for malaria parasitemia			X^e^					
Assess and record SAES			X^h^	X	X	X	X	X
Assess and record solicited AEs			X^h^	X	X			X^i^

^a^If not performed at previous visit.

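### The Day 7 question covers current symptoms only, so no structured solicited question reaches reactions that start after the Day 3 visit and resolve before Day 7, although the primary endpoint spans 7 days

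*Protocol article*

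**What the plan says.** Under Solicited Local and Systemic Reactions, the Day 3 visit has a look-back: participants are "asked about any events after vaccination on Day 0 and any current symptoms". The same sentence goes on to the later visit: "on Day 7, participants will be assessed for local and systemic reactions and will be asked about current symptoms". Five reactions are then listed for graded documentation on a standardized instrument: fever, injection site pain or tenderness, swelling, erythema and irritability.

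The outcome that these visits serve is defined over the whole week. Primary endpoint 1 in Table 1 is the "Proportion of participants who develop adverse events in the first 30 minutes after vaccination and for 7 days after vaccination". The reactogenicity rows of Table 3 are powered on "any grade 2 or greater solicited, systemic adverse events over 7 days following vaccination". Note on Timing says that solicited and unsolicited events through Day 7 will all be assessed and recorded.

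Table 4 marks the reactogenicity assessment and the recording of solicited events at both D3 and D7. The row for "Axillary temperature" is marked at screening, D0, D28 and early termination, and is blank at D3 and D7. Footnote d, attached to that row, gives an instruction that applies "before taking oral temperature".

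**The concern.** The look-back is written out for Day 3 and absent for Day 7, within one sentence. Read as written, the solicited record is a Day 0 to Day 3 period plus a snapshot at the Day 7 visit. That is not the cumulative 7-day proportion that Tables 1 and 3 describe.

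Two things are at stake. First, this is the primary safety endpoint, and a reaction that was not asked about at Day 7 cannot be reliably recovered at analysis. Second, each reactogenicity hypothesis in Table 3 is framed as no significant difference between regimens. Missing events in both arms lowers both proportions, shrinks the absolute difference and so makes the hypothesised result easier to reach.

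**Working it through.** **1. The passages side by side**

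| Place in the article | Period covered |
|---|---|
| Solicited reactions, Day 3 question | Vaccination to the Day 3 visit, plus current symptoms |
| Solicited reactions, Day 7 question | Current symptoms at the Day 7 visit |
| Table 1, primary endpoint 1 | First 30 minutes and 7 days |
| Table 3, reactogenicity rows | 7 days |
| Note on Timing | All events through Day 7 |

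The uncovered interval runs from the Day 3 visit to the Day 7 visit. Table 4 allows D7±1, so its length varies, and a visit held on Day 6 would also leave Day 7 unobserved. No diary or daily contact for this interval is described.

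**2. Reproducing the plan's power.** Inputs from Table 3: 45 per group (100 × 0.90 = 90, split 1:1), 10% v 33%, two-sided z-test with unpooled variance, 5% level.

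Power = Φ( |p2 − p1| / √[p1(1−p1)/n + p2(1−p2)/n] − 1.96 )

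- Variance: (0.10 × 0.90 + 0.33 × 0.67)/45 = 0.3111/45 = 0.00691, so SE = 0.0831.
- 0.23/0.0831 = 2.766, and 2.766 − 1.96 = 0.806.
- Φ(0.806) = 0.790.

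Exact enumeration of the same test gives 79.3%. The stated 80% is therefore reproduced within rounding, and the plan's power figure is not in dispute.

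**3. Effect of missed events.** Let f be the share of children with a grade 2 or greater systemic reaction whose only such reaction falls wholly between the two visits and is not recovered by another route. The documents give no value for f, so it is an assumption. With equal loss in both arms, the observable proportions are 0.10(1−f) and 0.33(1−f).

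| f | Proportions | Difference | Power at 45 v 45 |
|---|---|---|---|
| 0 | 10.0% v 33.0% | 0.230 | 79% |
| 5% | 9.5% v 31.4% | 0.219 | 76% |
| 10% | 9.0% v 29.7% | 0.207 | 73% |
| 20% | 8.0% v 26.4% | 0.184 | 66% |

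For f = 20%: (0.08 × 0.92 + 0.264 × 0.736)/45 = 0.2679/45 = 0.00595, SE = 0.0772, 0.184/0.0772 ≈ 2.385, and Φ(0.425) ≈ 0.66.

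All three reactogenicity rows (Groups 1 v 2, 3 v 4 and 4 v 5) use the same 10% and 33%, so the table applies to each.

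**4. Temperature.** Of the five solicited reactions, only fever and irritability are systemic, and the powered outcome is systemic. Table 4 schedules no temperature reading at either reactogenicity visit.

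**The case against.** A fair defence has four parts.

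*Other routes exist.* At Day 7, Table 4 lists reviews of medical history and concomitant medication as well as solicited event recording. Follow-up provides for unsolicited events at both visits and for illnesses seen at unscheduled visits. Definition of Adverse Event records vaccine-related events reported by telephone or at visits, with onset and resolution. Methods assesses non-serious events up to Day 28. A reader might infer from the Day 7 wording that events on Days 4 to 6 are never asked about or are lost altogether. The documents do not support that, because these routes may recover some of them. None of them, however, is a structured look-back with solicited grading, and Note on Timing states an aim without a question that achieves it.

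*The instrument is not shown.* The full case report form may contain a since-last-visit item that the article compresses. That is possible. But the article states the question for each visit and makes the two differ, so this is a conflict in the text rather than a detail left out.

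*Most reactions are early.* Potential Risks of Vi-Typhoid Conjugate Vaccine says that local reactions usually resolve within 48 hours of vaccination, so the Day 3 recall would catch many. This limits f. It also means that a similarly brief reaction starting on Day 4 or 5 could be over by Day 7, and the powered outcome is systemic rather than local.

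*The arms are treated alike.* Both follow the same visits, with blinded assessors through Day 7. Under equal loss the risk ratio is unchanged (33/10 = 26.4/8 = 3.3); only the absolute difference and the power fall. Bias from onset times that differ between regimens is conceivable, but nothing in the documents puts a figure on it.

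**Conclusion.** The point stands as an internal contradiction. The Day 7 question as written does not deliver the 7-day outcome in Tables 1 and 3 or the complete capture promised in Note on Timing. The direction is towards under-counting, a smaller absolute difference and the hypothesised result.

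The size is unknown. The fall in power from 79% to 76%, 73% or 66% is an illustration that rests on an assumed f of 5%, 10% or 20%, equal loss in both arms and the planned 45 per group. A reader might infer that the trial is underpowered by such an amount. The documents do not support that: they give no f, and the planned calculation is sound for the 7-day incidence that it assumes.

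The temperature points are secondary. The blank cells at D3 and D7 sit badly with fever as a solicited reaction, but a reading at Day 7 would not detect a fever that had already resolved, so they do not prove the recall gap. The oral/axillary mismatch is clerical.

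**What to change.** Reword the Day 7 rule so that the parent is asked about every solicited reaction since the Day 3 visit, with onset date, maximum grade and resolution, plus current symptoms. Maximum grade matters because a reaction that has eased by the visit could otherwise be graded only as it stands that day. Anchoring the question to the Day 3 visit also copes with the ±1 day window, except that a Day 6 visit still cannot cover Day 7; the text should say how that day is handled. If the data collection instrument already contains this look-back, correcting the sentence is enough.

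Reconcile Table 4 with the solicited reaction list by stating how fever is ascertained at D3 and D7, and make the temperature row and footnote d agree on the route of measurement.

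The cost is a few lines on an existing form at visits already scheduled, plus two temperature readings if they are added. The drawback is reliance on about four days of parental recall, similar to what the Day 3 visit already asks.
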